#### Adverse reactions

Adverse reactions are measured with a self-developed questionnaire. These reactions involve negative experiences of parents and/or children that are, according to parents, related to the care they received either in the brief parent training treatment arm or in the CAU arm. The questionnaire consists of six questions that ask parents whether they experience a decline in their trust in healthcare, (anxiety of) negative reactions from others (i.e., stigma), mental health issues, difficulties in relationships and activities, or any other difficulties or concerns that could be related to the care they received during the trial. For each question that applies to them, we ask parents to shortly elaborate on their experiences and indicate when these experiences happened. These answer options are based on the Medical and Psychological Events and Difficulties (MAPED) questionnaire that was used in the Online Parent Training for The Initial Management of ADHD referrals (OPTIMA) trial [71]. This outcome is measured at T3.

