## Methods

### Study design

In this two-arm multi-center randomized controlled trial, parents of children who experience behavioral difficulties in the home setting and were referred to a child mental healthcare center, are randomly assigned (1:1 ratio) to either (a) three sessions of brief behavioral parent training with optional booster sessions, or (b) CAU, as regularly provided by the involved mental healthcare centers. There are no restrictions regarding the type (e.g., psychoeducation, parent counseling and support, individual child therapy, medication) or duration of CAU, only the brief parent training investigated in this trial is not allowed. Both parents and children in the brief behavioral parent training group are not allowed to receive CAU until the first posttreatment assessment (T1). After that, CAU is allowed and parents can also make use of booster sessions with the therapist who provided the training.

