### Procedure

Parents in the brief behavioral parent training arm receive three sessions of behavioral parent training. The first two sessions take 120 min each and are planned one or two weeks apart. The third session takes 60 min and is planned one week after the second session. To take parents’ and therapists’ availability into account, some flexibility in planning is allowed as long as all three sessions are planned within six weeks with at least one week between two consecutive sessions. After the third session, parents wishing to receive additional support can receive CAU and/or booster sessions. The booster sessions take 60 min each and can be provided maximally once every four weeks up to one year after the last session of the brief behavioral parent training program. Booster sessions can be suggested by the therapist who provided the brief behavioral parent training or by other involved clinicians, or requested by parents themselves.

The trial contains four measurement occasions, see Fig. 1 for the participant timeline. T0 takes place after parents provide consent and are found eligible for participation, before randomization. The first posttreatment measurement (T1) takes place one week after the third session for parents in the brief behavioral parent training arm and eight weeks after T0 for parents in the CAU arm. The second posttreatment measurement (T2) takes place six months after T1 and the third posttreatment measurement (T3) takes place twelve months after T1. Participation in the trial therefore takes approximately 14 months in total. The care families receive at the child mental healthcare center may terminate sooner if they do not need or want care anymore.

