Other challenges concern potential hindrances for parents to participate. For instance, parents might find it difficult to complete all measurements during four occasions over an extended period of time (i.e., approximately 14 months). For several reasons, it can be difficult to stay dedicated to participate (e.g., motivational issues, time constraints). Besides, parents presumably take part in the trial hoping to receive the brief parent training and might therefore be disappointed when they are randomized into the CAU arm, which can cause their motivation for participation to decline. This might make parents who receive CAU more likely to drop out of the study. We anticipate this challenge by keeping parents involved in the measurements through frequent reminders, expressing the value of parents’ participation and thanking parents after each completed measurement. We also offer parents who consider quitting the study options to reduce the burden of the measurements (e.g., four instead of five daily phone calls, making less or no audio recordings) to possibly keep them involved for a longer period of time.

The results of the trial could have meaningful societal implications for children with behavioral difficulties and their parents. If we find the brief behavioral parent training to be more (cost-)effective than CAU, the treatment could be used in clinical practice to make parent training more accessible.

Quotient; EQ-5D-5L: EuroQol-5 Dimension 5-Level; KINDL-R: Health-Related Quality of Life Questionnaire (German abbreviation); MAPED: Medical and Psychological Events and Difficulties; METc: Medical Ethics Review Committee; ODD: Oppositional Defiant Disorder; PACHIQ-R: Parent–Child Interaction Questionnaire-Revised; PSOC: Parenting Sense of Competence Scale; PSS: Parental Stress Scale; QALYs: quality-adjusted life years; RR: Reward Responsiveness Questionnaire; SDQ: Strengths and Difficulties Questionnaire; SPSRQ-C: Sensitivity to Punishment and Sensitivity to Reward Questionnaire for Children; VCWE: Scientific and Ethical Review Board; V31, U: Vrije Universiteit Amsterdam.

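### Adverse reactions are asked once, looking back, at T3: families lost earlier give no harms data, and early reactions rest on recall of about a year

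*Protocol article*

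**What the plan says.** The Adverse reactions section describes a self-developed form of six questions, used in both arms. It concerns negative experiences that are, "according to parents, related to the care they received either in the brief parent training treatment arm or in the CAU arm". Its scope is the whole trial, since the last item covers "any other difficulties or concerns that could be related to the care they received during the trial". For each question that applies, "we ask parents to shortly elaborate on their experiences and indicate when these experiences happened". The timing is then fixed: "This outcome is measured at T3".

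The Procedure section places the assessments. In the training arm T1 "takes place one week after the third session for parents in the brief behavioral parent training arm"; in the CAU arm it is eight weeks after baseline. For both arms, "the third posttreatment measurement (T3) takes place twelve months after T1".

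Under Study design, families in the training arm may not receive CAU before T1. The section continues: "After that, CAU is allowed and parents can also make use of booster sessions with the therapist who provided the training".

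On retention, the Discussion foresees that families allocated to CAU may be disappointed, and adds: "This might make parents who receive CAU more likely to drop out of the study". The measures it lists against dropout are reminders, thanks and a lighter measurement load.

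**The concern.** A harms question asked only at the last visit has two weaknesses.

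The first is selection. The repeated outcomes have values at T0, T1 and usually T2, so a mixed model can use what a family gave before it left. Adverse reactions have no earlier value, so a family missing at T3 is missing altogether. If leaving has anything to do with a bad experience, the families with most to report are the ones not asked. If loss also differs by arm, the two arms are compared on differently selected remainders.

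The second is timing. T1 is the only post-treatment assessment at which the training arm should have received the three sessions and nothing else. By T3 boosters and CAU may have followed for up to a year. What happened during the training must then be recovered from memory.

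At stake is the harms description that would accompany a recommendation to use the program in practice. The primary effectiveness result is not affected.

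**Working it through.** The point turns mainly on when the form is given. The arithmetic shows how much this could matter.

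**Denominator.** The article gives no figure for adverse reactions, so the planned sample size is the reference. Its inputs (Sample size calculation) are *f* = 0.125, two groups, three measures, *r* = 0.60 and α = 0.05. For the within-between interaction, the noncentrality is λ = *f*² × N × m / (1 − *r*), with m the number of measures and degrees of freedom 2 and 2(N − 2). N = 84 gives power 0.801 and N = 83 gives 0.796, so 84 is reproduced. Then 84 × 1.10 = 92.4, rounded up to 93. The figure is sound and serves here only as a denominator.

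**Recall interval.** Inputs are from Procedure: three sessions within six weeks, at least one week between consecutive sessions, T1 one week after session 3, and T3 twelve months (52 weeks) after T1.
- Shortest, session 1 to T3: 2 + 1 + 52 = 55 weeks.
- Longest, session 1 to T3: 6 + 1 + 52 = 59 weeks.
- Session 3 to T3: 1 + 52 = 53 weeks.

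**Care that may intervene.** Boosters are limited to one every four weeks for up to a year after session 3, so at most about 52 / 4 = 13, with CAU possible alongside. This is a ceiling; expected use is not stated.

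**Families with no harms data.** Silent families = 93 × dropout before T3. The article gives no such rate, so 10% to 30% is assumed.
- 10%: 93 × 0.10 = 9.3, about 9 families.
- 30%: 93 × 0.30 = 27.9, about 28 families.
- Unequal loss, for illustration (10% in training, 30% in CAU, about 46.5 families per arm): 46.5 × 0.90 = 41.9 against 46.5 × 0.70 = 32.6 responders.

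The pilot's 14.2% would give 93 × 0.142 = 13.2 families. It comes from a non-randomized pre-post study of 28 families and does not measure loss over 14 months.

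**How many reactions could be missed.** Suppose leavers have twice the risk of stayers (assumption). With dropout d, the share of all affected families found among leavers is 2d / [(1 − d) + 2d], whatever the risk in stayers.
- d = 0.10: 0.20 / 1.10 = 18%.
- d = 0.30: 0.60 / 1.30 = 46%.

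If leavers had the same risk as stayers, the share would simply equal d. The loss would then cost precision but not distort the rates.

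**What can still be attributed.** CAU is barred in the training arm until T1, and parents are asked for the date of each experience. A reaction correctly dated before T1 therefore belongs to the three sessions. A reaction starting after T1 could be a late effect of training, an effect of a booster or an effect of CAU, and the date alone does not decide between them.

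**The case against.** The strongest reply is that the form already asks when each experience happened, and that CAU is barred in the training arm before T1. A reader might infer from the T3 timing that harms of the three sessions cannot be separated from later care at all. The article does not support that: separation is possible for reactions dated before T1. What remains is dependence on dating after more than a year.

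Second, the randomized comparison is the program with optional boosters against CAU. A T3 question about all care received fits that strategy, so the mixture of treatments is not in itself a fault. This stands, and it is why T3 should be kept.

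Third, a reader might infer that the trial could wrongly declare the training harmless because harmed families leave. The only dropout the article predicts by arm is in CAU, and the reason given is disappointment with allocation. If CAU reactions were lost selectively, the training arm would tend to look relatively worse, not falsely safe. Nothing in the document predicts dropout from the training arm because of harm.

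Fourth, stopping care is not leaving the study. Care may end early, and the article does not say that measurement then ends. Such families can still answer at T3, so the loss concerns study dropouts only.

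Fifth, behavior, well-being, parenting stress and the parent–child relationship are measured at T1, as is satisfaction with the training. These could show early worsening, but they do not ask about reactions attributed to care.

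Finally, a contact at withdrawal may be described in the full protocol. Silence on that is not held against the article. The stated T3-only timing is a rule, however, and the point rests on it.

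**Conclusion.** The point holds as a limited but real weakness of a stated design choice. One retrospective form at T3 collects nothing from families lost to the study before then, and the article itself expects that loss may be larger in CAU. For those who remain, placing early reactions with the three sessions relies on recall and dating 55 to 59 weeks after session 1, and reactions starting after T1 cannot be cleanly apportioned.

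The size depends on a dropout rate that is not given: about 9 to 28 of 93 families at an assumed 10% to 30%. How far this would bias the comparison depends on whether leavers differ in risk, which is also unknown; the 18% to 46% share assumes a doubled risk. The direction of any bias between arms cannot be fixed from the document. The change is worth making because it is cheap and because missing answers cannot be recovered at analysis.

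**What to change.** Give the same six-question form at T1 as well as T3 in both arms, and once, by phone or e-mail, to any family that withdraws from the study. Report by arm how many families answered on each occasion.

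Use the T1 and exit answers to describe early reactions. State beside them that CAU families are only eight weeks from baseline at T1 and may have had little care to react to, so a low CAU count at T1 is not evidence that CAU is safer. Keep T3 for the comparison of the full strategies. The existing question on timing lets a reaction reported at both T1 and T3 be counted once.

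The cost is a few minutes for parents at T1, where 30 to 45 minutes of questionnaires are already completed, and one contact per withdrawing family. No new instrument is needed. Families already past T1 when the change is made would be covered only by the exit contact and T3, and the report should say so.

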### Sample size calculation

Based on our previous study that found medium-sized short term effects on daily ratings of behavioral difficulties compared to waitlist (range of Cohen’s *d* = 0.35 to *d* = 0.66, [33]) and studies showing medium-sized parenting intervention effects on behavioral difficulties using parent-report rating scales [19, 20, 25, 36, 72], we estimate the effect of our brief behavioral parent training program as compared to CAU to be at least small (*d* = 0.25).

A power analysis has been performed using G*Power software [73]. Based on an effect size of *d* = 0.25 (*f* = 0.125), two groups and three repeated measures (T0, T1, T2 for short term effectiveness), with *r* = 0.60 between-measurement relation, a power of 0.80 and α = 0.05, we need at least 42 participants per group, resulting in a total of 84 participants. Given that the data are clustered, we increased the sample size with 10% [74], resulting in a total of 93 participants. This is in line with the number of participants in similar studies comparing behavioral treatments to CAU (e.g., [36]).

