To address this need, this randomized controlled trial evaluates the effectiveness of a brief and individually tailored behavioral parent training program with optional booster sessions for children with behavioral difficulties. The program is based on intervention elements that were effective in reducing children’s behavioral difficulties in the broader literature and our earlier work: antecedent techniques (i.e., stimulus control techniques) and consequent techniques (i.e., contingency management techniques) [22, 31, 32]. Antecedent techniques are aimed at changing child behavior by manipulating the antecedents of this behavior (e.g., by setting clear rules and providing structure) and consequent behavioral techniques are aimed at changing child behavior by manipulating their consequences (e.g., by praising desired behavior and ignoring undesired behavior). In a recent microtrial in which we evaluated the efficacy of antecedent and consequent techniques, both sets of techniques were found to reduce behavioral problems of children with ADHD in brief (i.e., two sessions) behavioral parent training, of which antecedent techniques were especially effective in decreasing inattention [33]. This microtrial also showed that the magnitude of effects of a brief program (i.e., medium-sized effects) was similar to those of traditional, longer programs on reducing child behavioral difficulties [23, 33, 34].

Building upon the findings of our microtrial, the brief behavioral parent training of the present trial consists of two sessions in which antecedent and consequent techniques are combined and a third session aimed at the evaluation and maintenance of applying the learned techniques. To prevent relapse and the possible use of other, more intensive and expensive treatments, parents can receive booster sessions in the first year after the brief training. Similar to the microtrial, the behavioral parent training is individually tailored by letting parents select four target behaviors they want to address in the training and by creating an individually tailored intervention plan based on the functional analysis (see [33]). A non-randomized pilot study (*N* = 28) preceding the present trial indicated a relatively low dropout rate (14.2%), high treatment feasibility and parent and clinician satisfaction, and a reduction of children’s behavioral difficulties from pre to post intervention [35].

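### The stated 80% power for d = 0.25 does not hold: f = d/2 appears to have been entered for a time-by-condition interaction, where power with 84 to 93 families is about 24–26%

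*Protocol article*

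**What the plan says.** All of the following is in the protocol article.

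- **Target effect (Sample size calculation):** "we estimate the effect of our brief behavioral parent training program as compared to CAU to be at least small (*d* = 0.25"). It is a comparison of the two arms. The support cited is a waitlist comparison with d from 0.35 to 0.66, together with studies using parent-report rating scales.
- **Inputs (same section):** "Based on an effect size of *d* = 0.25 (*f* = 0.125), two groups and three repeated measures", the occasions being T0, T1 and T2, "with *r* = 0.60 between-measurement relation", power 0.80 and α = 0.05. The software is G*Power; the procedure is not named.
- **Result (same section):** "we need at least 42 participants per group, resulting in a total of 84 participants". A 10% increase for clustering follows, "resulting in a total of 93 participants". No allowance for loss of outcome data is mentioned.
- **Timing (Allocation to study arms):** families are randomized after the T0 measurement.
- **Test (Statistical analysis):** a mixed model in which the time-by-condition interaction carries the comparison of change between arms.

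**The concern.** Three of the printed figures (d = 0.25, 84 families, power 0.80) appear not to fit together under the inputs given. Halving d gives Cohen's f when two groups are compared on a single mean. In a within-between interaction, f measures how much the arm difference varies over time, so the same d yields a much smaller f.

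As printed, the article tells readers that the trial can be expected to detect a small advantage over usual care. If it cannot, a non-significant result could be misread as evidence against a small benefit. The article links implementation of the training to superiority over usual care (Ethics and dissemination), so that misreading would have consequences.

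**Working it through.** **Inputs.** From the Sample size calculation section: d = 0.25, f = 0.125, two groups, m = 3 occasions, r = 0.60, α = 0.05. From Allocation to study arms: T0 precedes randomization, so the expected arm difference at T0 is zero. Assumed throughout: equal variances, the same correlation between all occasions, no loss of outcome data.

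**Step 1: reproduce 84.** For the within-between interaction with two groups, λ = f²·N·m/(1 − r), with df = m − 1 and (N − 2)(m − 1).
- f = 0.125, N = 84: λ = 0.015625 × 84 × 3/0.40 = 9.84; df = 2 and 164; power 0.801.
- N = 82: power 0.791. So 84 is the smallest even total.
- Clustering: 84 × 1.10 = 92.4, rounded up to 93.

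Between-arm alternatives that do not give 84:

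| Option | Total N for 80% |
|---|---|
| Between-arm main effect, f = 0.125, λ = f²·N·m/(1 + (m − 1)r) | 372 |
| Interaction, 4 occasions | 72 |
| Interaction, 2 occasions | 104 |
| Two-sample comparison, d = 0.25 | 504 |

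**Step 2: the interaction f implied by d = 0.25.** Take half the arm difference at each occasion, centre over occasions, and take the root mean square.
- Differences (0, d, d): halves (0, d/2, d/2), mean d/3, deviations (−d/3, d/6, d/6). Mean square = (d²/9 + d²/36 + d²/36)/3 = d²/18. Hence f = d/√18 = 0.25/4.243 = 0.059.
- Differences (0, d/2, d): f = d/√24 = 0.051.
- In reverse, f = 0.125 with (0, d, d) needs d = 0.125 × 4.243 = 0.53.
- Over all patterns with arm differences within ±0.25 SD at the three occasions, the largest f is 0.118, and that requires the sign to reverse. The entered 0.125 is out of reach for the stated d.

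**Step 3: power for d = 0.25 on the interaction.**
- Sustained, N = 84: λ = (0.0625/18) × 84 × 3/0.40 = 2.19; power 24.0%. A simulation of 20,000 trials also gave 24.0%.
- Sustained, N = 93: λ = 2.42; power 26.2%.
- Linear build-up: 18.9% at 84 and 20.5% at 93.
- 80% power for the sustained pattern needs about 372 families before any clustering allowance.
- With a sustained d = 0.53 and N = 84, simulated power is 80.0%.

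**Step 4: does another between-arm analysis rescue the claim?** Two-sided power for d = 0.25:

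| Analysis | N = 84 | N = 93 |
|---|---|---|
| T1 alone, unadjusted | 21% | 22% |
| Change T0 to T1 | 24% | 27% |
| Between-arm main effect, f = 0.125 | 26% | 29% |
| T1 adjusted for T0 | 29% | 32% |
| Mean of T1 and T2, minus T0 | 31% | 34% |
| Mean of T1 and T2, adjusted for T0 | 40% | 44% |
| Mean of T1, T2 and T3, adjusted for T0 | 46% | 50% |

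If the 10% is what clustering costs, 93 families are worth 93/1.10 ≈ 84.5 independent ones, so the N = 84 column is the fairer one.

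**The case against.** **The procedure is inferred.** The article does not say which G*Power option was used. With two groups the within-factor test has the same λ and degrees of freedom, so it too would return 84. This stands as a caution, but it does not help the plan: that test does not compare the arms. The main-effect option, where f = d/2 is legitimate, needs 372 families and has 26–29% power here.

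**Power depends on the analysis and the effect pattern.** A reader might take about a third as the ceiling, from a single baseline-adjusted T1 comparison. The document does not support that limit. It plans no such contrast; it names the time-by-condition interaction over several occasions. Across analyses and patterns the range is about 19% to 50%.

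**Attrition.** A reader might infer that the plan's own pilot implies 14.2% loss and hence about 80 analysable families (93 × 0.858 = 79.8), fewer than 84. The Background reports that pilot dropout alongside feasibility and satisfaction, without saying that outcome data were lost. Under intention-to-treat, families who leave the training but are still measured stay in, and a mixed model uses partly observed families. The Discussion says only that disappointment at allocation to usual care "This might make parents who receive CAU more likely to drop out of the study", gives no rate, and lists countermeasures. So 14.2% loss is an illustration, not a figure from the plan.

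**The sample is not unreasonable for a larger effect.** The 0.53 SD it can detect lies within the cited 0.35 to 0.66. That is partial comfort only, because that range is against waitlist and this trial's comparator is usual care.

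**Conclusion.** The concern holds for the conversion and the power claim. The 84 follows from f = 0.125 used as an interaction effect, but that f does not represent d = 0.25 in arms equal at baseline. On the planned interaction, power for a sustained d = 0.25 is about 24% at 84 families and 26% at 93, against the stated 80%; a linear build-up gives 19–21%. The most favourable analysis examined reaches 50%, and only if clustering costs nothing. The detectable sustained difference at 80% power is about 0.53 SD with an effective 84 families.

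These figures rest on r = 0.60, equal variances and correlations, and complete outcome data. The choice of G*Power option is an inference, but the shortfall does not depend on it, since no between-arm analysis tried comes near 80%. The absence of an attrition allowance is secondary: loss of outcome data would lower power further, by an amount the document does not allow one to fix.

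**What to change.** Keep 93 families. Delete the conversion of d = 0.25 to f = 0.125 and restate the power for the interaction test named in the Statistical analysis section, for example:

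> With 93 families (effective number about 84 after the 10% clustering allowance) and no loss of outcome data, the time-by-condition interaction over T0 to T2 has 80% power for a sustained standardised difference of about 0.53. Power for d = 0.25 is about 24%.

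Add that a non-significant result will be interpreted from the confidence interval and not as evidence against a small benefit. Say that the 10% covers clustering only. If a loss scenario is shown, label it as an assumption (14.2% loss would leave about 80 of 93). Name the G*Power procedure used.

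The cost is wording only, with no added families or measurements. The downside is that the stated power becomes less favourable.

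### The step from 84 to 93 families is assigned wholly to clustering, so the stated 80% power assumes no attrition; at the pilot's 14.2% loss it would be about 75–79%

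*Protocol article*

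**What the plan says.** The Sample size calculation section of the protocol article gives the whole chain. The inputs are "Based on an effect size of *d* = 0.25 (*f* = 0.125), two groups and three repeated measures" (T0, T1 and T2), "with *r* = 0.60 between-measurement relation, a power of 0.80 and α = 0.05". The result is "we need at least 42 participants per group, resulting in a total of 84 participants". The last step is "Given that the data are clustered, we increased the sample size with 10% [74], resulting in a total of 93 participants". No attrition rate or allowance appears in the section.

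Two other places bear on attrition. The Background says of the non-randomized pilot (N = 28) that it "indicated a relatively low dropout rate (14.2%), high treatment feasibility and parent and clinician satisfaction". The Discussion notes that four measurement occasions over about 14 months may be hard for families to complete. It adds that parents allocated to care as usual may be disappointed: "This might make parents who receive CAU more likely to drop out of the study". It answers with reminders and a lighter measurement load for families who think of leaving, not with a sample-size allowance.

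The Statistical analysis section plans an intention-to-treat analysis by multilevel (mixed) models that accommodate missing data.

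**The concern.** Eighty-four is exactly the number that the calculation requires, and the nine families above it are all assigned to clustering. On the protocol's own account, no margin is left for families who miss T1 or T2, although the article itself reports or anticipates dropout. A reader will take 93 enrolled families to mean 80% power. If the trial finds no difference from care as usual, that null result will be judged against a power figure that holds only with complete follow-up.

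**Working it through.** **Inputs.** From the Sample size calculation section: f = 0.125, two groups, m = 3 occasions, r = 0.60, alpha = 0.05, 84 families, plus 10% for clustering, total 93. From the Background: 14.2% pilot dropout and, from cited literature, 26% premature termination of parent training (used only as an upper sensitivity value). The 20% is an assumption.

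**1. The protocol's figures.** For the group-by-time interaction in a repeated-measures F test, λ = f² × N × m / (1 − r), with df1 = 2 and df2 = 2(N − 2).

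- N = 84: λ = 0.015625 × 84 × 3 / 0.40 = 9.84; power 0.801.
- N = 83: power 0.796. So 84 is the smallest N that reaches 0.80.
- Clustering: 84 × 1.10 = 92.4, rounded up to 93.

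Both figures reproduce. Once the clustering allowance is spent, 93 families are worth 84 independent ones, and no margin remains.

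**2. Attrition under the planned mixed model.** Assume equal correlations of 0.60, unit variance, 84 effective families, and the same between-arm effect at T1 and T2, scaled so that complete data give λ = 9.84.

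If a fraction L leaves before T1, T0 is still used. Per arm of n families, the variance of the change from T0 to the mean of T1 and T2 is [0.44 / (1 − L) + 0.16] / n. Here 0.44 = (1 + 0.60)/2 − 0.60² and 0.16 = (1 − 0.60)². With L = 0 this is 0.60 / n, so

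λ = 9.84 × 0.60 / [0.44 / (1 − L) + 0.16].

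For later loss, λ comes from the generalized least squares information summed over the patterns T0 only, T0 and T1, and all three.

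| Loss, both arms | Timing | λ | Power |
|---|---|---|---|
| 0 | – | 9.84 | 0.801 |
| 14.2% | all before T1 | 8.78 | 0.751 |
| 14.2% | half before T1, half before T2 | 9.15 | 0.770 |
| 14.2% | all after T1 | 9.52 | 0.787 |
| 20% | all before T1 | 8.32 | 0.727 |
| 26% | all before T1 | 7.83 | 0.699 |

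For unequal loss before T1 (14.2% in the training arm, an assumed 20% under care as usual), the bracket averages (0.673 + 0.710)/2 = 0.691. Then λ = 9.84 × 0.60 / 0.691 = 8.54 and power is 0.739.

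**3. Complete cases, for comparison.** At 14.2%, 93 × 0.858 = 79.8 families remain, and 79.8 × 84/93 = 72.1 effective families give power 0.733. At 20% and 26% the figures are 0.700 and 0.662.

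**4. If clustering cost nothing.** Multiplying λ at 14.2% loss by 93/84 gives 9.72, 10.14 and 10.54 for the three timings, with power of about 0.80, 0.81 and 0.83.

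**5. Shape of the effect.** If the effect at T2 is half that at T1, the range at 14.2% is 0.747 (all before T1) to 0.801 (all after T1). If the effect at T1 is half that at T2, it is 0.747 to 0.756.

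**The case against.** - **The mixed model softens the loss.** This stands. A reader might infer power of 0.73 at 14.2% loss and 0.66 at 26%, but those are complete-case figures and the trial plans no complete-case analysis. The mixed model uses partial records, so the loss at 14.2% is about 1 to 5 points, not 7. It cannot recover T1 and T2 outcomes that were never observed.
- **Clustering may cost little.** Families are randomized individually within centres, and constant therapist or centre intercepts largely cancel from a time-by-condition contrast. If clustering cost nothing, the nine families would cover 14.2% attrition (step 4). But the protocol gives clustering as its reason for adding them, and it reports no intraclass correlation or cluster size that would free them for another purpose.
- **The dropout figures are not follow-up losses.** This stands. A reader might take 14.2% as the trial's own loss rate. The Background does not define it, and it rests on 28 families. The 26% concerns stopping training, and under intention to treat that does not by itself remove outcome data. Both serve here as assumptions.
- **The protocol does not predict higher dropout under care as usual.** This also stands. A reader might infer that it does, but the Discussion says only that this might happen, gives no rate, and lists steps to prevent it.

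**Conclusion.** The point holds as an omitted allowance, not as an arithmetic error: 84 and 93 are correct for the inputs stated. Eighty per cent power for 93 families requires complete T0–T2 data. If 14.2% are lost in both arms and the clustering allowance is needed in full, power under the planned model is about 0.75–0.79. Early loss of 20% or 26% brings it to about 0.73 or 0.70.

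These figures assume that pilot dropout carries over to missing outcomes, equal correlations of 0.60, and a similar effect at T1 and T2. If the effect fades by T2 and families leave only after T1, almost nothing is lost.

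All of them are conditional on f = 0.125. In this test, with equal effects at T1 and T2, that f corresponds to a between-arm difference in change of about 0.53 SD: 84 families give λ = a² × 42 / (2 × 0.60) = 9.84, so a = 0.53. This is not the 0.25 SD that the stated d suggests. That is a separate and larger matter, so none of these percentages should be read as power for a 0.25 SD difference.

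**What to change.** Keep 93 families and amend the Sample size calculation section to say:

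- that 80% power assumes no attrition between T0 and T2;
- power with attrition as a conditional range, for example about 75–79% at 14% loss and about 70–73% at 20–26% loss before T1, under the planned mixed model with the 10% clustering allowance and f = 0.125;
- that the 14% is taken from the pilot, and whether the pilot figure counted families leaving treatment or leaving the study.

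If the conversion from d to f is corrected, recompute the range with the new f. The cost is one or two sentences and a slightly less favourable power statement. No extra families or procedures are needed.
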